## Abstract

**Introduction::**

Hypertrophic scars are a common disease in plastic surgery, which is the reaction of skin connective tissue to trauma beyond the normal range. Although scholars around the world have explored the tissue structure and formation mechanism of HS for decades, they are not satisfactory the result of. No effective treatment has been found. Therefore, the search for safe and effective treatments for HS has always been the focus of medical attention and research. Acupuncture therapy has a definite effect on HS and has unique advantages.

**Methods/design::**

In this study, we will use our own front-to-back clinical research method. We plan to include 120 young and middle-aged female patients who meet the diagnostic criteria for HS. The untreated HS of the enrolled patients will be used as blank controls. The intervention group will be given acupuncture treatment. The assessment of scar area, color, hardness, thickness, itching and pain will be recorded for 30 days of treatment.

**Discussion::**

This trial may provide evidence regarding the clinical effectiveness, safety, and cost-effectiveness of Acupuncture for patients with HS.

**Trial registration::**

ClinicalTrials.gov, ChiCTR2000032624, Registered on 04 May 2020.

## Introduction

1

Hypertrophic scars (HS) are a common type of cosmetic lesions and are common diseases in the aesthetic department. With the improvement of people's quality of life, there is also increasing concern about HS. HS can occur at any age, but it often occurs between 10 and 35 years old. Young people are susceptible to the disease, especially during adolescence and pregnancy. The incidence of men and women is similar.^[1]^ Previous studies have shown that women have a higher morbidity rate, which may be a bias caused by women who have higher cosmetic requirements and are more likely to go to the clinic than men. The incidence of HS varies greatly among races.^[2]^ The incidence is higher among blacks and people with darker skin. HS can occur in all races. The incidence of black and Mongolian races is relatively high, estimated to be between 4% and 16%, which is 5 to 15 times that of Caucasians. Differences between regions have a significant impact on the incidence of HS.^[3]^ Europeans living in the tropics are more susceptible to illness than Europeans living in the temperate zone. HS occur in the anterior sternum, back, neck, neck, deltoid region, beard area, and earlobe, and are rare in the upper eyelid, penis, scrotum, areola, palms, soles, and cornea.^[4]^ HS brings great difficulty to the physical and mental recovery of patients. The clinical manifestation of this disease is that the scar is obviously higher than the surrounding normal skin, and the local thickening and hardening. The mechanism of scar formation is currently not fully understood. It is generally believed that due to the inflammatory response of the body, fibroblasts and myofibroblasts proliferate and synthesize a large amount of collagen and matrix, which in turn causes collagen metabolism and arrangement abnormalities.^[5]^ Although scholars from all over the world have explored the organizational structure and formation mechanism of HS for decades, there have been no satisfactory results. No effective treatment has been found.

Common treatment methods for HS currently include surgery, drug therapy, laser therapy, radiation therapy, compression therapy, silicone gel membrane, gene therapy and so on.^[6]^ Among the drug treatments, Western medicine treatment mainly targets extracellular matrix-targeted drugs (including glucocorticoids, pyridone, collagenase, etc.), cell-targeted drugs (including 5-FU, bleomycin, retinoic acid, Colchicine, etc.), biological microenvironment targeting drugs (including growth factor regulating drugs, immunomodulators, anti-inflammatory drugs, anti-allergy drugs) and other directions. Western medicine has achieved obvious results in the local treatment of HS, but it still cannot solve the problem of recurrence of purpura.^[7]^ Traditional Chinese medicine (TCM) has a unique understanding of the disease and rich clinical experience. TCM has a unique understanding of HS. TCM believes that HS is due to the deficiency of positive qi after skin trauma, and the toxic poison stagnate on the surface of the skin, which gradually causes the phlegm and congestion of the body to form on the surface, thereby forming scars. And it is related to their own constitution. Some TCM experts hold that this is related to long-term dampness in the body or dampness of the lungs and stomach, coupled with skin trauma, stagnation of blood and blood stasis, and eventually keloids are formed.^[8]^ Therefore, in the treatment of HS, TCM usually starts with the methods of promoting blood circulation, removing blood stasis, tonifying pain, resolving phlegm and dispersing knots, orally combined with external treatment, or supplemented with acupuncture and point injection. TCM has a good clinical effect on the treatment of this disease. TCM has a definite curative effect on prevention and treatment of HS, and has unique advantages. Oral Chinese medicine, external application of Chinese medicine, acupuncture and moxibustion, and integrated Chinese and Western medicine treatment can be selected. Among them, acupuncture combined with oral medication is not only effective in treating the disease, but also has high psychological acceptance. Moreover, it is safe and secure, with little toxic and side effects, and easy to operate. Acupuncture therapy is easy to learn and use, economical and easy to promote. However, there are few research reports on the treatment of this disease by acupuncture. In this study, acupuncture will be used as an intervention to treat HS, and its efficacy will be objectively evaluated. In this study, we will use our own front-to-back clinical research methods to evaluate the clinical efficacy and related indicators of young and middle-aged female patients who meet HS, and then look for an objective and effective treatment of HS. We aim to provide an objective basis for the clinical efficacy of acupuncture treatment of HS.

## Methods/design

2

### Study design and settings

2.1

This study will be conducted at the Second Affiliated Hospital of Shaanxi University of Chinese Medicine. This protocol was written and based on Standard Protocol Items: Recommendations for Interventional Trials guidelines. The participants will be informed about the research, procedures, risks, and benefits by [name] (author of this protocol). If they agree, they will sign an informed consent form. Only those participants who read and agree to the protocol and who sign the informed consent form will take part of the study, following the schedule described in Figure 1.

**Figure 1 F1:**
[figure not shown]
Study design flow chart.

### Participants

2.2

The subjects of this study will be included in the outpatient and hospitalized patients from the Department of Plastic Surgery of the Second Affiliated Hospital of Shaanxi University of Chinese Medicine, and meet the diagnostic criteria for HS. The research subjects gave informed notification and signed the “*Informed Consent for Pathological Scars Clinical Research*”.

#### Diagnostic criteria

2.2.1

We will refer to the diagnostic criteria for pathological scars in “*Plastic Surgery*”. We will refer to the “Beauty Surgery” published by the People's Medical Publishing House (Beijing, China). The specific standards are as follows:

(1)HS occurs in various parts of the human body and occurs 4 weeks after trauma.(2)The lesion is limited to the scope of the wound; the early color is bright red and hard; it often shows excessive keratinization, ulceration and contracture; the texture and bulge of the mature stage are beyond the original damage range, and the mature stage is from June to December.(3)Consciously itching and burning pain in different degrees.(4)Symptoms can disappear after several months to 1 to 2 years, and gradually become dark brown, tending to be stable.

In addition, we will refer to the *“Vancouver Scar Scale”* combined with accompanying symptoms to develop scoring criteria, and then grade the severity of HS. The scale has a total score of 21 points. A higher score indicates more severe scarring. Mild: Total points ≤7. Moderate: 7 <total points ≤15. Severe: Total points> 15.

#### Inclusion criteria

2.2.2

This study will be conducted in China. Patients will be recruited from Plastic surgery departments of the Second Affiliated Hospital of Shaanxi University of Chinese Medicine. We will enroll participants based on the following inclusion criteria:

(1)It meets the diagnostic criteria for HS;(2)The scar area is less than or equal to 6 cm^2^.(3)Female patients of 16 ≤ age ≤ 40 years old;(4)The time for the formation of fatigue marks exceeds 3 months;(5)Those who have voluntarily signed the informed consent;

#### Exclusion criteria

2.2.3

Patients will be excluded if they meet the following criteria:

(1)People with allergies and allergies to experimental drugs;(2)Ages <16 or >40 years;(3)Patients with renal cancer, bladder tuberculosis, urinary stones;(4)Patients with other malignant tumors;(5)Patients with blood system diseases, coagulation dysfunction and autoimmune diseases;(6)Patients with severe cardiovascular disease, cerebrovascular disease, hematopoietic system disease, and neuropathy;

#### Conditions for participants to suspend and withdraw from the clinical trial

2.2.4

Researchers participating in clinical trials should carefully record the reasons for the suspension of the trial and the relationship with the clinical trial. It is necessary to clearly record the unwillingness of the subjects to continue the clinical trials, put forward the reasons for withdrawing from the clinical trials, and record the evaluation indicators at the time of discontinuation in detail.

(1)Those who cannot adhere to treatment;(2)Allergic reactions or serious adverse reactions during the test, the test should be suspended:(3)Those who have not been treated strictly according to the plan;(4)People who withdrew from the study on their own.

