### Interventions

2.3

The participants included in the observation will be self-controlled, and each patient randomly selected 3 different scar treatment areas at the same site as observation specimens.

Control group: Take the untreated pathological scars of the participants as blank control. This group will not give any intervention.

Intervention group: Before the treatment, we will carry out strict physical examination and dermatological examination on the patient, and make sure that the patient has no obvious contraindications, and then carry out acupuncture treatment.

(1)Patient position: Choose according to the patient's scar location (supine position, lateral position or sitting position, etc.).(2)Operation steps: first disinfect the scar area and perform acupuncture in a circular shape on the local scar area of the patient. Needle retention time is 30 min, and the needle is moved twice during the needle retention process. The number of acupuncture depends on the size of the scar area of the affected area, with a minimum of 4 and a maximum of 15, each needle is about 3 cm apart, and the needle insertion is 1 cm to 1.5 cm. At the end of the 30-minute needle retention time, hold the hand on the eye of the needle with a medical swab and proceed in sequence.(3)Course of treatment: once every two days, 30 days as a course of treatment. Observe the scars every 15 days of treatment (Fig. 2).

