**Figure 2 F2:**
[figure not shown]
SPIRIT figure for the schedule of enrollment, interventions, and assessments.

Research requirements:

(1)Aseptic operation to prevent infection.(2)Acupuncture is prohibited when the patient is fasting or fatigued; acupuncture is prohibited in cases of local skin ulcers, tumors, fresh wounds, etc.(3)Avoid greasy, spicy food, coffee, strong tea and other diets.(4)Women can’t acupuncture during lactation and pregnancy. People with allergies should use acupuncture with caution.

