### Statistical analysis

2.7

Data management uses EXCEL software to build a database, double entry, check for outstanding values, and lock. Statistical analysis will be performed using SPSS 25.0 software for statistical analysis. The normality of the measurement data is tested. The data obeying the normal distribution is Student's *t* test, which is expressed by mean ± standard deviation. The data not obeying the normal distribution is rank sum test. And marginal homogeneity test; count data are expressed by rate and composition ratio, and comparison is performed by chi-square test; repeated measurement data are expressed by mean ± standard deviation, intra-group comparison is performed by analysis of variance of repeated measurement data, and inter-group comparison is by multivariate analysis of variance (MANOVA). *P* ≤ .05 indicates that the difference is statistically significant.

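### Withdrawing women after allocation for not keeping to the treatment plan falls mainly on the acupuncture group if the groups are parallel, and can bias the comparison

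*Protocol article*

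**What the plan says.** Section 2.2.4 of the protocol article sets out when participants suspend or withdraw from the trial. Item (1) is "Those who cannot adhere to treatment", item (3) is "Those who have not been treated strictly according to the plan" and item (4) is "People who withdrew from the study on their own". The reasons and the evaluation indicators are to be recorded when the participant stops. Section 2.4 schedules observations on days 15, 30, 45 and 60. Nothing in 2.2.4 provides for those visits once a woman has been withdrawn.

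Of the control, Section 2.3 says: "This group will not give any intervention". The acupuncture group is needled once every two days for 30 days.

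The design is described in two ways. Section 2.5 plans 60 patients in each group, and Section 2.6 has an envelope opened to settle a patient's group, which implies parallel groups. The Abstract and Section 2.3 instead make each participant her own control, with untreated scars of the same women as the blank control.

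The list of research requirements in Section 2.3 rules out "acupuncture during lactation and pregnancy". The exclusion criteria in Section 2.2.3 mention neither condition, and Section 2.2.2 enrols women aged 16 to 40.

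**The concern.** Adherence is observed after allocation and may be related to outcome. Removing women because of it breaks the balance that allocation provides, and the damage is greatest when the rule can operate in one group only. With an untreated parallel control there is almost nothing to adhere to, so items (1) and (3) bear mainly on the acupuncture group. If women who find needling painful or unhelpful are more likely to stop, those who remain will look better than the group that was allocated, and an ineffective treatment could appear to work.

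This is more than a detail left to an analysis plan. The rule governs who stays in the trial, and no later analysis plan can recover visits that were never made.

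The pregnancy and lactation mismatch could add to the imbalance. Section 2.3 places the contraindication check under the intervention group, before treatment, and does not say that it comes before the envelope is opened. A woman barred only from needling could therefore be allocated first and then lost from that group alone.

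**Working it through.** **The plan's own figures.** Section 2.5 gives a difference of 11 points, alpha 0.05, power 95% and 49 per group, raised by 20% to 60. No SD is stated. Working backwards (two-sided, normal approximation), SD = 11 × √(49/2) / (1.960 + 1.645) = 15.1. The 49 can be neither confirmed nor refuted: an SD of 12 to 20 gives 31 to 86 per group. The dropout step is close: 49 × 1.2 = 58.8, so 59, and 49/0.8 = 61.25, so 62, against the stated 60. The 20% allowance is not split by group. It serves below only as a convenient size for the loss.

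**Parallel reading, no true effect.** The inputs are 60 per group (Section 2.5), a fraction q removed from the acupuncture group only (assumed), and a correlation ρ between removal and poor outcome (assumed). In units of the outcome SD,

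bias = ρ × φ(z_q) / (1 − q).

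For q = 0.20, z_q = −0.8416 and φ(z_q) = 0.280, so bias = ρ × 0.280/0.80 = 0.35ρ. With 48 women left against 60, the standard error is √(1/60 + 1/48) = 0.194. The two-sided type I error is P(Z > 1.96 − bias/0.194) + P(Z < −1.96 − bias/0.194).

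| q | ρ | Bias (SD) | Type I error |
|---|---|---|---|
| 10% | 0.3 to 0.5 | 0.06 to 0.10 | 6% to 8% |
| 20% | 0 | 0 | 5% |
| 20% | 0.3 | 0.10 | 8% |
| 20% | 0.5 | 0.17 | 15% |
| 20% | 1 | 0.35 | 44% |
| 30% | 0.3 to 0.5 | 0.15 to 0.25 | 11% to 24% |

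The row with ρ = 1 means that exactly the worst 20% leave. The formula holds the SD at 1, although truncation narrows the spread of those who remain. A simulation of 20,000 null trials with a t test allows for this and gives about 50% in that row. At ρ = 0.5 it gives 15% and at ρ = 0.3 it gives 9%, so the approximation is adequate in the moderate cases.

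**Self-controlled reading.** A withdrawn woman takes her treated and untreated areas with her. Let r be the correlation between the two areas. If removal depends on the woman as a whole, both areas shift equally and the bias is about 0. If it depends on the treated area,

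bias = ρ × (1 − r) × φ(z_q) / (1 − q).

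With q = 0.20 and ρ = 0.5 this is 0.175 × (1 − r): 0.12, 0.07 and 0.02 SD for r = 0.3, 0.6 and 0.9. A simulation gives the same values.

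**The case against.** The strongest objection is the design. On the self-controlled description every woman is treated, and a withdrawn woman leaves both sides of the comparison. A reader might infer from 2.2.4 that the rule can remove women from the acupuncture group only. The documents do not support that. It presumes parallel groups, and even then a control woman who obtained treatment might be judged off plan, while item (4) applies to anyone. *Mainly* is as far as the text goes, and only on the parallel reading.

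A reader might also infer that withdrawn women are dropped from the analysis. The protocol does not say so. It records indicators at discontinuation, and the analysis set may be defined in a plan not shown. This stands, but it does not remove the problem, because a value at discontinuation is not a day 30 or day 60 outcome.

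A third tempting step is that MANOVA, named in Section 2.7 for the between-group comparison, deletes every woman with a missed visit and so favours acupuncture further. Section 2.7 says nothing about missing data. If complete records were required, an assumed 5% missing independently at each of four visits would leave 0.95⁴ = 81%. That costs precision and by itself favours neither group.

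The direction is not certain either. With no link between stopping and outcome there is no bias, and women who stop because they have improved would reverse it.

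Finally, allergy might be offered as another one-sided loss. Section 2.2.3 excludes "People with allergies and allergies to experimental drugs", while Section 2.3 says "People with allergies should use acupuncture with caution". The two need reconciling, but if the exclusion is applied the caution removes nobody after allocation.

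**Conclusion.** The point holds in a conditional form. Section 2.2.4 makes inability to adhere and deviation from the treatment plan conditions for leaving the trial after allocation. On the parallel-group reading this falls mainly on the acupuncture arm, as written ends later follow-up there, and can bias the comparison, plausibly towards acupuncture.

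With no true effect and an assumed 20% lost from that arm alone, moderate correlations of 0.3 to 0.5 give 0.10 to 0.17 SD and a type I error of about 8 to 15%. The 0.35 SD and roughly 50% obtained when exactly the worst 20% leave are an upper bound for a loss of that size, not an expectation. On the self-controlled reading, with the same 20% and a correlation of 0.5, the bias is about 0 to 0.12 SD.

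The documents give neither the fraction lost in one arm nor its correlation with outcome. All these sizes illustrate the problem and also assume that the women removed do not enter the comparison. The pregnancy and lactation mismatch between Sections 2.2.3 and 2.3 is real, but that it would lead to withdrawals after allocation is an inference. The change should be made because it is cheap and sound under either design.

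**What to change.** - In Section 2.2.4, record items (1) and (3) as protocol deviations rather than as grounds for leaving the trial. This concerns follow-up only and does not touch decisions to stop needling.
- Continue the scheduled day 15 to 60 assessments in women who stop needling, unless they refuse.
- Analyse all allocated women in their allocated group using all available visits, for example with a mixed model for repeated measures. Report a per-protocol result as a sensitivity analysis only.
- Reconcile the parallel-group and self-controlled descriptions, and fit the analysis to the design that is kept.
- Reconcile Section 2.2.3 with the restrictions on needling in Section 2.3. Check whatever restrictions result in every woman before the envelope is opened.

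The cost is some protocol wording and a few follow-up visits in women who have stopped needling. The estimated effect may be smaller, because women who did not adhere now count in it.

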### Interventions

2.3

The participants included in the observation will be self-controlled, and each patient randomly selected 3 different scar treatment areas at the same site as observation specimens.

Control group: Take the untreated pathological scars of the participants as blank control. This group will not give any intervention.

Intervention group: Before the treatment, we will carry out strict physical examination and dermatological examination on the patient, and make sure that the patient has no obvious contraindications, and then carry out acupuncture treatment.

(1)Patient position: Choose according to the patient's scar location (supine position, lateral position or sitting position, etc.).(2)Operation steps: first disinfect the scar area and perform acupuncture in a circular shape on the local scar area of the patient. Needle retention time is 30 min, and the needle is moved twice during the needle retention process. The number of acupuncture depends on the size of the scar area of the affected area, with a minimum of 4 and a maximum of 15, each needle is about 3 cm apart, and the needle insertion is 1 cm to 1.5 cm. At the end of the 30-minute needle retention time, hold the hand on the eye of the needle with a medical swab and proceed in sequence.(3)Course of treatment: once every two days, 30 days as a course of treatment. Observe the scars every 15 days of treatment (Fig. 2).

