### Sample size calculation

2.5

The sample size for this trial is based on an expected mean difference between groups of 11 points of the Constant–Murley questionnaire, which is the minimum clinically important difference. To detect this difference between both treatments, with a value of a = 0.05 (probability of committing a type I error) and a statistical power of 95%, a minimum of 49 patients per group is needed. This minimal sample size estimate has been increased by 20% after considering the potential dropouts, finally including 60 patients for each group. Accordingly, the proposed experimental hypothesis is that there will be a difference of at least 11 points in the Constant—Murley questionnaire in the intervention group versus the control group. The sample size was determined using the Stata SE software.

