### Randomization and blinding

2.6

(1)The concealment of random schemes: After the scheme design is completed, the random schemes are enclosed in a sequence-encoded, sealed, light-tight envelope. Then it is handed over to the person in charge of the subject, after screening qualified cases, the envelope is opened to determine the grouping.(2)The recorder fills in the case report form with basic data and observation of the patient's local and systemic symptoms.(3)Unified production of various documents.(4)Check and confirm the correctness and completeness of all research data records and reports and case report forms, and ensure consistency with original data.

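### The protocol describes at least two incompatible designs, self-controlled scars and separate groups of 60 patients, so the allocated unit and the control are undefined

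*Protocol article*

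**What the plan says.** Two descriptions stand side by side in the protocol article.

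**Self-controlled.** The abstract says "we will use our own front-to-back clinical research method", and the introduction (section 1) and discussion (section 3) repeat this. The abstract adds: "The untreated HS of the enrolled patients will be used as blank controls". Section 2.3 says "The participants included in the observation will be self-controlled", and continues: "each patient randomly selected 3 different scar treatment areas at the same site as observation specimens". It does not say which of the three areas is needled and which, if any, is left alone. The efficacy indices in sections 2.4.1 and 2.4.2 are percentage changes from before to after treatment.

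**Separate groups of patients.** The abstract plans for 120 women. Section 2.5 sizes a difference between groups at a minimum of 49 patients in each and ends with "finally including 60 patients for each group". Section 2.6 has sealed envelopes: "after screening qualified cases, the envelope is opened to determine the grouping". Section 2.4 records indicators for each group of patients at days 15, 30, 45 and 60.

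**Analysis.** Section 2.7 lists Student's t test, rank sum test, marginal homogeneity test, chi-square test, repeated-measures ANOVA within groups and MANOVA between groups. It does not name a comparison of treated with untreated areas within a patient.

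**The concern.** If every woman is her own control, 60 patients per group has no meaning. If 60 women receive nothing, those women are not self-controlled. This is a conflict in the stated text, not a detail that an article leaves to a fuller document.

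Two things are at stake. The first is what the comparison protects against. The protocol says that these scars improve without treatment. Section 2.2.1 has symptoms disappearing after several months to 1 to 2 years. Section 3 has the scar shrinking and softening in the decline period that follows a peak at 6 months. Section 2.2.2 asks only that the scar be more than 3 months old, so an enrolled scar can be regressing during the 60 days of observation. Without a concurrent untreated scar, that regression would be credited to acupuncture.

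The second is the unit of analysis. With positively correlated areas, an unpaired analysis of within-patient pairs overstates the standard error. Treating several areas of one patient as independent in a parallel-group trial understates it.

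**Working it through.** **1. Which design does the sample size belong to?** Inputs from section 2.5: difference 11 points, alpha 0.05, power 95%, 49 per group, 20% increase. No SD is given, so 49 cannot be strictly reproduced and the SD has to be back-solved. For two independent groups, n = 2 × (SD × (z_alpha/2 + z_power) / difference)². With z values 1.960 + 1.645 = 3.605:

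SD = 11 × √(49/2) / 3.605 = 15.1 (two-sided).

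Putting 15.1 back gives 49 per group. For the 20% step, 49 × 1.2 = 58.8, so 59, and 49 / 0.8 = 61.25, so 62. The stated 60 lies between them, and 2 × 60 = 120, the total in the abstract. The plan is therefore sized as two independent groups of patients.

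**2. What would the self-controlled design need on the same inputs?** For pairs, n = (SD × √(2(1 − rho)) × 3.605 / 11)². The within-patient correlation rho is not in the document, so it is varied as an assumption.

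| rho (assumed) | evaluable patients, paired | evaluable patients, two groups |
|---|---|---|
| 0 | 49 | 98 |
| 0.3 | 35 | 98 |
| 0.5 | 25 | 98 |
| 0.7 | 15 | 98 |

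These figures only illustrate the contrast. The 11 points are on the Constant–Murley questionnaire, which is not this trial's outcome scale; that is a separate defect.

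**3. Precision from the 120 patients.** This step does not need the SD. After 20% loss, 120 × 0.8 = 96 patients remain.

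- Two groups, 48 v 48: SE = SD × √(2/48) = 0.204 SD.
- 96 pairs: SE = SD × √(2(1 − rho)/96).

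| rho (assumed) | SE, 96 pairs | 0.204 SD divided by this |
|---|---|---|
| 0 | 0.144 SD | 1.4 |
| 0.3 | 0.121 SD | 1.7 |
| 0.5 | 0.102 SD | 2.0 |
| 0.7 | 0.079 SD | 2.6 |

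One treated and one untreated area per patient are assumed here. The role of the third area in section 2.3 is not stated.

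**4. Can the sections be reconciled by reading?** If the envelope allocates areas within a patient, section 2.6 can be squared with section 2.3, but section 2.5 (60 patients in each group) and section 2.4 (groups of patients) cannot. If the envelope allocates patients, sections 2.4 to 2.6 agree, but the abstract and section 2.3 do not. Each reading leaves at least one section wrong.

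**The case against.** The strongest defence is that less is in conflict than first appears, and much of it stands.

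- A reader might count three designs: before-after, within-patient and two groups. The abstract puts the before-after method and the patients' own untreated scars in one paragraph, so these may be one design described twice. The text supports at least two designs.
- A reader might infer 0, 120 or 60 concurrent controls depending on the section. No section states 0 or 120; those counts follow only from a chosen meaning of untreated.
- A reader might conclude that self-control leaves the envelope nothing to do. It could allocate areas within a patient, and section 2.3 already uses the word group for scars. What is missing is a statement of the unit.
- A reader might suppose that the operator chooses which area is needled. The text does not say so. It says that three areas are randomly selected, but not how treatment is assigned among them.
- Section 2.5 is weak evidence of intent, because it is written around a questionnaire used nowhere else in the protocol and does not mention randomisation. But its 60 + 60 matches the 120 in the abstract, and section 2.4 also speaks of groups of patients.
- Section 2.7 is mixed. The marginal homogeneity test is for paired data and the MANOVA is between groups, so this section does not settle the matter for either design.
- The study flow chart and the schedule figure are not shown and may define the groups. They could not remove the conflict in the text.

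None of this reconciles section 2.3 with section 2.5.

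**Conclusion.** The point holds as a contradiction between a self-controlled design (abstract, sections 1, 2.3 and 3) and separate groups of patients (sections 2.4 to 2.6). The allocated unit and the control are undefined. The sample size is that of two independent groups, and section 2.7 fits neither design fully. It must be resolved before recruitment, because the choice decides whether spontaneous regression is separated from the effect of treatment.

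That last consequence is conditional: it follows if untreated means before treatment, which the document neither states nor excludes. The size in precision is a factor of 1.4 to 2.6 between the designs, for assumed correlations of 0 to 0.7, 20% loss and one pair per patient. A reader might quote a twofold gap, but that figure holds only at a correlation of 0.5, which the document does not give.

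**What to change.** State one design in the abstract and in sections 1, 2.3, 2.5, 2.6, 2.7 and 3, and align section 2.4 with it. Two options are coherent.

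(a) **Parallel groups.** Each envelope allocates a patient, 60:60, to acupuncture or no intervention. The scar area or areas to be scored are fixed before the envelope is opened. The before-after and self-controlled wording is deleted. The analysis compares independent patients, and if several areas per patient are scored it accounts for their clustering.

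(b) **Within-patient.** Each envelope allocates which of the patient's areas is treated and which stays untreated, with the role of the third area stated. Both treated and untreated areas are scored at every visit. The 60 per group is replaced by a number of patients recalculated for paired data. The analysis is paired or clustered by patient.

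Under either option, the efficacy conclusion rests on treated versus concurrent untreated scars, not on before-after change in treated scars alone.

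The cost is low now, because section 2.9 says that recruitment has not started and that the plan has yet to go to the ethics committee. It is more than a change of wording: section 2.7 needs revision under both options, and option (b) also needs a new sample size.
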